### Setting and participants

Over a six-month period participants will be recruited from the private community practice of a single orthopaedic shoulder surgeon ([name]) in Melbourne, Australia. Recruiting patients from a single shoulder surgeon eliminates the potential confounding factors of surgical skill, technique, experience and postoperative care. All surgery will be performed by this surgeon.

All eligible patients who fulfil the selection criteria during the recruiting period will be invited to participate. Inclusion criteria will be all patients aged 18 to 90 who will be undergoing rotator cuff repair, subacromial decompression or excision of the distal clavicle by the surgeon. Exclusion criteria will be: (i) grade IV gleno-humeral arthritis of the shoulder undergoing operation diagnosed on arthroscopy (ii) preoperative shoulder stiffness (iii) concomitant surgical procedure except for rotator cuff repair, subacromial decompression, distal clavicular resection, debridement, bursectomy, synovectomy or biceps tenodesis (iv) superior labral tear from anterior to posterior (SLAP) repair (v) inability to answer questions by phone (vi) poor English language skills.

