#### Outcome assessment

Baseline data collected from participant will include sex, age, dominant arm, shoulder side undergoing operation, history of diabetes mellitus and present treatment for diabetes mellitus, third party compensation status, history of depression, time since diagnosis of depression, whether participant is presently receiving treatment for depression and whether and type of previous surgery the participant has had on the shoulder undergoing operation (see Additional file 1).

Preoperatively participants will have range of motion assessed and be asked to complete a questionnaire encompassing pain, analgesia, sleep and mood (see Additional file 2). Range of motion of the shoulder will be assessed for each of the following planes of motion: active elevation, passive glenohumeral abduction with stabilisation of the scapula, passive external rotation in adduction and passive internal rotation in 90°, or maximal, abduction. This will be done using a goniometer. Average pain, worst pain at rest whilst seated with the arm at the side, worst pain with movement and worst pain at night over the last 24 h will be assessed using a visual numerical rating scale (NRS). The NRS pain scale is an 11 point scale where 0 = no pain and 10 = worst possible pain. Participants will be asked to detail the types of analgesia, dosage and treatment they have received in the last 24 h. Sleep will be assessed using a visual NRS sleep scale where 0 = worst possible sleep and 10 = best possible sleep. Participants will be asked what type and dosage of mediation (if any) they have taken to help them sleep in the last 24 h. Last, participants will be provided with a Patient Health Questionnaire – 9 (PHQ-9) that will assess their mood and depressive symptoms over the past two weeks and they will be classified as depressed or not depressed according to the DSM-IV criteria for a major depressive episode [35]. The PHQ-9 has a sensitivity of 98 % and specificity of 80 % for major depressive disorder when using the cutoff of 11 points or greater and allows for stratification of depression severity [35, 36].

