Postoperatively participants will be clinically followed up at multiple time points. The operating surgeon will assess them at both their first and final postoperative consultations. The first consultation around the time of suture removal, and the second consultation three months after the operation. In addition the investigator will contact them by phone postoperatively on days two, five and seven and additionally at weeks four, seven and ten. At both postoperative surgeon clinical assessments the participants will asked to complete the PHQ-9. This will assess their mood over the previous two weeks. At their final postoperative consultation the range of motion of their treated shoulder will also be assessed. The senior surgeon will determine clinically whether or not the patient has ‘postoperative stiff shoulder’.

During each of the follow up phone calls, participants will be asked to complete the same pain questionnaires as preoperatively with the use of a verbal NRS and to detail the types of analgesia, dosage and any other treatment they have received in the last 24 h. The preoperative sleep assessment, using a verbal NRS, will be preformed postoperatively at these times. Participants will be asked what type and dosage of mediation (if any) they have taken to help them sleep in the last 24 h. Lastly patients will be asked to describe their mood over the past 24 h and also describe any events or stressors that may have impacted upon their pain, sleep or mood. This will be recorded on specifically designed form (see Additional file 3). Therefore each participant will have six phone assessments over the three months.

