### Analysis

The incidence of postoperative stiff shoulder will be determined using the treating surgeon’s clinical diagnosis informed by the Buchbinder criteria of restriction of motion of greater 30° in two or more planes of shoulder motion [40].

Patient demographics, baseline range of motion, pain, sleep and depression scores and outcome data will be presented for both outcome groups (postoperative stiff shoulder and no postoperative stiff shoulder).

The principal analysis will involve assessing whether or not a relationship exists between average pain scores and development of postoperative stiff shoulder. This will be by determining if there is a significant difference of the mean of the “average pain scores over the last 24 h” between both outcome groups at each recorded time point and over predetermined periods (first week postoperatively, first month postoperatively and from week four to ten postoperatively), adjusted for multiple comparisons using the Holm’s step down procedure [41].

Secondary analysis will assess depression and its relationship with PSS. A history of depression diagnosis as well as active depression at each time point, as assessed by the PHQ-9, will be assessed for an association with a diagnosis of PSS adjusted and not adjusted for baseline depression, and adjusted for multiple comparisons using the Holm’s step down procedure [41].

This study will also report the incidences of postoperative stiff shoulder after rotator cuff repair as well as subacromial decompression and excision of the distal clavicle not in association with rotator cuff repair.

Finally a series of range of motion criteria will be used to objectively determine a range of incidences of PSS in the same cohort (Table 1).

**Table 1 Tab1:** Criteria for diagnosing postoperative stiff shoulder

Criteria for diagnosing postoperative stiff shoulder
Clinician’s diagnosis
Range of motion thresholds in two planes, both required • Active elevation <100 degrees AND • Passive external rotation <30 degrees
Range of motion thresholds in two planes, at least one required • Active elevation <100 degrees OR • Passive external rotation <30 degrees
Restricted range of motion compared to contralateral side, at least two planes • Restriction of >30 degrees in TWO or more planes of movement
Restricted range of motion compared to contralateral side, at least three planes • Restriction of >30 degrees in THREE or more planes of movement

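### The Table 1 threshold criteria have no baseline condition, so some shoulders already below a cut-off before surgery may be counted as incident stiffness, mainly under the either-plane rule

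*Protocol article*

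**What the plan says.** The Analysis section of the protocol article states that "a series of range of motion criteria will be used to objectively determine a range of incidences of PSS in the same cohort", and Table 1 lists the criteria. Besides the clinician's diagnosis and two comparisons with the other shoulder, there are two threshold rules. One requires both cut-offs. The other is headed "Range of motion thresholds in two planes, at least one required" and reads "Active elevation <100 degrees OR" "Passive external rotation <30 degrees". Neither mentions motion before surgery.

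On timing, Outcome assessment says: "At their final postoperative consultation the range of motion of their treated shoulder will also be assessed". No other postoperative measurement of motion is described.

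On baseline, the same section says "Preoperatively participants will have range of motion assessed", and the planes listed include "active elevation, passive glenohumeral abduction with stabilisation of the scapula, passive external rotation in adduction". Both threshold planes are therefore measured before surgery. The Analysis section presents baseline motion by outcome group but does not make it part of any criterion.

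On eligibility, Setting and participants excludes "preoperative shoulder stiffness", with no plane and no number of degrees.

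**The concern.** One reading against an absolute cut-off gives the proportion below it at that time. It is an incidence only if everyone counted was above the cut-off at the start. The exclusion is the only safeguard, and nothing ties it to 100 or 30 degrees.

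The third aim in the Background is to compare rates across criteria, and the Background also promises sensitivity and specificity against the surgeon's diagnosis. A deficit carried over from before surgery can raise a threshold rate. Where the surgeon does not diagnose stiffness, it also counts as a false positive and lowers that criterion's specificity. Part of the difference between criteria could then reflect preoperative status rather than how well each detects postoperative stiffness.

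**Working it through.** **The plan's own figure.** The only computed figure is the sample size. A two-sided two-sample t-test with difference 2, SD 2.20, alpha 0.05, power 0.80 and 10% incidence gives 11 stiff plus 99 not stiff = 110 (power 0.809 at that split), and 110 × 1.2 = 132. It reproduces and is not in question. Below, 110 serves only as the number evaluable.

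**What the exclusion covers.** The Background defines the condition as motion limited both actively and passively, and calls this suitable for postoperative stiffness too. If the exclusion is read that way:
- *Both cut-offs required.* A shoulder meeting this rule before surgery is limited in an active and a passive measure, so the exclusion should largely remove it.
- *Passive external rotation alone under 30 degrees.* Most such shoulders would plausibly be excluded, but without a stated number overlap cannot be ruled out.
- *Active elevation alone under 100 degrees.* Pain or cuff weakness can cause this without passive restriction. That is clinical reasoning, not a statement in the article. Such a shoulder is not stiff under the Background definition, need not be excluded, and meets the either-plane rule if still low at three months.

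**Possible size.** Let
- p = true risk of newly meeting the criterion among shoulders above the cut-offs before surgery;
- b = share of enrolled shoulders below a cut-off before surgery;
- s = share of those still below at three months.

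Apparent incidence = (1 − b) × p + b × s, and the net excess over p is b × (s − p).

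The documents give neither b nor s, so both are assumed. For p, 10% is borrowed from Sample size; 4.9% and 23.2% are the ends of the published range in the Abstract.

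At p = 10%:
- b = 0: 10.0%, no bias.
- b = 2%: 0.098 + 0.02 × s, so 10.3% (s = 0.25) to 11.8% (s = 1).
- b = 5%: 0.095 + 0.05 × s, so 10.8% to 14.5%.
- b = 10%: 0.090 + 0.10 × s, so 11.5% to 19.0%.

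| p | b = 0 | b = 5%, s = 0.25 to 1 | b = 10%, s = 0.25 to 1 |
|---|---|---|---|
| 4.9% | 4.9% | 5.9% to 9.7% | 6.9% to 14.4% |
| 10% | 10.0% | 10.8% to 14.5% | 11.5% to 19.0% |
| 23.2% | 23.2% | 23.3% to 27.0% | 23.4% to 30.9% |

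In cases, with N = 110, p = 10% and s = 0.5, the net excess is 110 × 0.05 × 0.4 = 2.2 at b = 5% and 110 × 0.10 × 0.4 = 4.4 at b = 10%, against 11 expected. The carried-over cases themselves number 110 × 0.05 × 0.5 = 2.75 and 110 × 0.10 × 0.5 = 5.5. The net is smaller because those shoulders no longer contribute new cases at 10%.

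Restricting to shoulders above both cut-offs before surgery returns p in every row, by construction.

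**The case against.** The strongest reply is that the third aim is to apply differing criteria as they stand to one cohort. The Background itself expects some of them to over- or under-diagnose. If an absolute cut-off flags shoulders that the surgeon does not call stiff, its poor specificity is a finding of the study. This stands as a reason to keep the full-cohort rates. It also tells against giving each criterion its own at-risk denominator in the main comparison, since differences between criteria would then partly reflect different denominators. It does not justify calling a three-month proportion an incidence, nor does it show how much of a criterion's excess was present before surgery.

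A second reply is that stiff shoulders are excluded. That largely protects the rule requiring both cut-offs. A reader might infer from Table 1 that every shoulder below 100 or 30 degrees before surgery will be counted as a new case. The documents do not support this: many such shoulders should never be enrolled, and nothing shows how many remain.

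A third is that baseline motion is not ignored, because it is tabulated by outcome group. That is correct, but it does not enter any criterion. How a secondary table is conditioned could be left to an analysis plan. Here, however, the article itself fixes the case definitions and names the result an incidence.

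**Conclusion.** The point holds as a possibility, not a certainty. The threshold criteria lack a baseline condition, are read once at about three months, and are not matched by the exclusion. Some carried-over deficits may therefore be counted as incident, mainly under the either-plane rule through active elevation.

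The size rests on assumed values of b and s, and on a 10% risk that the article does not link to this rule. The bias is zero if the exclusion in practice covers the cut-offs. The excess is positive only when the persisting share exceeds the new-case risk.

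The consequence is confined to the comparison of criteria. The surgeon-diagnosed incidence, the principal pain analysis, the depression analysis and the sample size do not use the thresholds. This is an inexpensive improvement to a stated aim, not a flaw in the main results.

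**What to change.** In the Analysis section:
1. Keep the full-cohort rates for the comparison of criteria, but label the two threshold rates as the proportion meeting the criterion at three months.
2. Apply the two threshold criteria to the preoperative measurements and report how many participants met each.
3. Add the rates for all Table 1 criteria, with sensitivity and specificity against the surgeon's diagnosis, in the one common subset that met neither threshold before surgery. A single subset keeps the denominator the same across criteria.

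The cost is a few sentences and one added table. The preoperative values needed to form the subset are already collected. The downside is a slightly smaller denominator in the added analysis: from 110 evaluable, 110 × 0.95 = 104.5 (about 104 or 105) if 5% start below a cut-off, and 110 × 0.90 = 99 if 10% do.

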## Discussion

The aims of the study will be to provide greater insight into the incidence of PSS post rotator cuff repair and report incidences of PSS post subacromial decompression and/or excision of the distal clavicle not in association with rotator cuff repair. A further aim is to identify whether increased pain levels can be used as a marker of patients who may benefit from early intervention to prevent or manage PSS. and to assess whether depression is a risk factor for the development of PSS. Finally we aim to compare and contrast the incidences of PSS determined by different objective clinical criteria in the same patient cohort.

The results of this trial we anticipate will contribute to our clinical understanding of the development of the postoperative stiff shoulder therefore improving clinical care and peri-operative information for patients. In addition it will provide a platform for discussion of how to objectively define this condition with the aim of assisting the development of a consensus definition.

Strengths of our prospective study will include the involvement of a single surgeon with set surgical protocols, statistical power to detect a clinically meaningful difference in pain scores, and the ability to assess a temporal relationship between pain, depression and postoperative stiff shoulder through the use of a cohort study. In addition the study will have the ability to determine the incidence rate of PSS after rotator cuff repair as well as in patients having a subacromial decompression without rotator cuff repair and also those undergoing an excision of the distal clavicle not in association with rotator cuff repair. These figures are absent from the current literature.

## Abbreviations

NRS: numerical rating scale
PHQ-9: patient health questionnaire – 9
PSS: postoperative stiff shoulder
SD: standard deviation
SLAP: superior labral tear from anterior to posterior
